**Figure 1 fig1:**
[figure not shown]
Flow chart of data acquisition. T_0_, baseline assessment; T_1_, post-treatment outcome assessment; T_2_–T_4_, 4-month follow-up assessment.

During the treatment period, therapists will meticulously document each therapy session to ensure comprehensive data collection and analysis. This documentation includes recording severe potential adverse events (e.g., hospital admissions, suicidality) and specific features of the EMDR treatment, such as the therapeutic target, the bilateral stimulation technique used, and the subjective units of distress. Additionally, therapists will complete a questionnaire regarding their prior experience with EMDR and the frequency with which they treat patients with chronic pain.

The documentation process involves capturing detailed information on critical aspects of each EMDR session, including the patient’s distress levels and beliefs about their symptoms before and after the session. Therapists will also assess and record the patient’s acceptance of the psychological model and provide a brief summary of the session’s content.

By systematically documenting these elements, therapists will create a comprehensive data set that facilitates detailed analysis of the processes and outcomes of EMDR therapy. This rigorous approach enhances the validity of the trial and contributes to the growing evidence base for EMDR therapy in the treatment of chronic pain and associated psychological conditions.

### Sample

2.4

The network includes both patients and therapists, each meeting specific inclusion and exclusion criteria to ensure the reliability and validity of the study outcomes.

#### Inclusion criteria

2.4.1

Therapists: Must have completed formal training in psychotherapy and possess an officially recognized certification in EMDR therapy. Only therapists who meet these stringent professional qualifications are included to ensure the consistency and quality of EMDR delivery.Patients: Eligible patients are those who have sufficient proficiency in the German language, as effective communication is essential for the therapeutic process and for providing informed consent. Patients must report experiencing chronic pain and must be commencing therapy with a therapist participating in this network. The prerequisite is that the patients have already started psychotherapy, but the planned EMDR treatment has not yet taken place as part of this therapy but is planned in the further course of therapy. Completed previous therapies, including EMDR, are not an exclusion criterion, but will be documented systematically. Patients must be at least 18 years old, with no upper age limit, and be able to give informed consent.

#### Exclusion criteria for patients

2.4.2

Severe Psychiatric Comorbidity: Patients exhibiting severe psychiatric conditions that impair their ability to provide informed consent, including suicidality and psychosis spectrum disorders, are excluded. These conditions can significantly interfere with the patient’s ability to participate effectively in the study and can complicate the assessment of EMDR’s efficacy.Language Proficiency: Patients lacking sufficient proficiency in the German language are excluded to ensure clear communication and accurate understanding of the therapy and study requirements. This criterion is critical for maintaining the integrity of the therapeutic process and the reliability of the study data.

By establishing these inclusion and exclusion criteria, the study aims to create a representative sample of patients with chronic pain that can provide robust and reliable data on the efficacy of EMDR therapy in treating chronic pain. The dual focus on therapists’ qualifications and patients’ characteristics ensures a high standard of therapeutic intervention and data collection. This methodological rigour is essential for drawing valid conclusions about the therapeutic benefits of EMDR in this specific patient population.

### Sample size calculation

2.5

The sample size calculation for the present exploratory and feasibility evaluation within the ‘EMDR Pain Therapy Network’ is primarily based on the need to obtain meaningful data on the feasibility and efficiency of the network structures. Considering the aim of assessing the feasibility of a possible future randomised controlled trial, a minimum number of 20 therapists will be recruited, each of whom should enrol at least 10 patients in the trial. This results in a total of at least 200 patients.

This sample size is appropriate for the following reasons:

It enables a comprehensive assessment of the efficacy and side effect profiles of EMDR therapy for chronic pain.It is suitable for testing the feasibility of an accompanying evaluation in the outpatient setting, including documentation quality and patient satisfaction.

The results of the evaluation of the initial sample of 200 patients will be crucial in planning a larger multicentre trial. They should show whether the network is able to recruit enough patients and provide high quality data, and whether the therapeutic practices within the network are sufficiently standardised to conduct a randomised controlled trial.

It is important to note that this number of cases does not have to be the definitive end of the trial. Rather, once this initial target number has been reached, an interim analysis should be carried out to assess the logistical and administrative aspects of the study implementation, in addition to the scientific aspects. On this basis, an adapted or expanded recruitment strategy can be developed for the next phase of the study.

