The network not only investigates the effectiveness and prediction of treatment response to EMDR in real clinical settings but also establishes a robust foundation for future randomised controlled multicentre studies. The systematic training and experience of therapists in the use of EMDR, along with standardised data collection methods, facilitate the development of a pool of qualified professionals essential for further clinical research. This pool of therapists will be a valuable resource for future studies aimed at testing the efficacy of EMDR on a larger scale and advancing its implementation in the treatment of complex pain disorders in clinical practice.

The network promotes the use of EMDR in pain therapy without commercial interests. Free working materials and free participation in the network support open science and patient-centred treatment. This approach aims to remove barriers to access and facilitate the dissemination of this effective therapy. This promotes a collaborative and inclusive model that benefits therapists and patients alike.

In summary, the developed framework promises to improve the understanding of the therapeutic effect of EMDR on chronic pain. It enables longitudinal analyses that describe the course of treatment success and identify individual differences in outcomes. This provides the basis for personalised treatment strategies that are tailored to the individual needs of patients with chronic pain in order to optimise therapeutic outcomes and improve quality of life.

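### A single treated cohort without a comparator can describe change during psychotherapy that includes EMDR, but not the efficacy of EMDR that the article claims for its 200 patients

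*Protocol article*

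**What the plan says.** Section 2.5 (Sample size calculation) builds the number from recruitment: "a minimum number of 20 therapists will be recruited, each of whom should enrol at least 10 patients in the trial", and "This results in a total of at least 200 patients". It calls the evaluation exploratory and describes the number as "primarily based on the need to obtain meaningful data on the feasibility and efficiency of the network structures". The first of its two supporting reasons is nevertheless: "It enables a comprehensive assessment of the efficacy and side effect profiles of EMDR therapy for chronic pain".

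Section 2.4.2 promises robust efficacy data from the sample and adds: "This methodological rigour is essential for drawing valid conclusions about the therapeutic benefits of EMDR in this specific patient population". Section 4.2 evaluates the effectiveness of EMDR by Cohen's d with t-tests, analyses response by logistic regression on the patient and therapist global impressions of change, and looks for predictors of therapy success by regression in the same patients. The Discussion says of the framework: "This provides the basis for personalised treatment strategies that are tailored to the individual needs of patients with chronic pain".

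On the design, section 2.3 has therapists choosing which patients to report, EMDR given within regular psychotherapy, and T1 taken when patient and therapist end the therapy. Section 2.4.1 states: "The prerequisite is that the patients have already started psychotherapy, but the planned EMDR treatment has not yet taken place". No control group, waiting list, randomisation or external comparator is described.

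**The concern.** Efficacy, effectiveness of EMDR and therapeutic benefit of EMDR are causal terms. They need some account of what would have happened without EMDR, and this design supplies none. Psychotherapy is running before EMDR starts and continues around it, other treatments may change, and chronic pain fluctuates. T1 has no fixed date and depends on how the therapy goes. A change score adds all of this together. The global impression ratings have the same limit, because a patient who improves for any reason will report improvement.

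The predictor analyses have a narrower version of the problem. In one treated group, a baseline variable associated with outcome is a prognostic factor under treatment. The data cannot show whether it also changes the effect of EMDR, which is what tailoring treatment would require.

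At stake is how the results will be read. With 200 patients a modest non-specific change is likely to be statistically significant, and the article as worded invites the reader to take it as an effect of EMDR.

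**Working it through.** **1. The plan's own figure.** 20 therapists × 10 patients = 200. The stated minimum is reproduced. It is a recruitment target: section 2.5 gives no effect size, SD, alpha, power or dropout, so there is no efficacy calculation to check.

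**2. What a change from T0 contains.**

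| Component | Basis in the article | Separated from EMDR by the design? |
|---|---|---|
| EMDR | 2.2, 2.3 | – |
| Other psychotherapy | already started (2.4.1); EMDR embedded in it (2.3) | No |
| Co-treatment | recorded (Table 1, 2.2); not named in the effectiveness analysis (4.2) | No |
| Natural course | T1 at end of therapy, no fixed interval (2.3) | No |
| Regression to the mean | possible with therapist selection (2.3); size unknown | No |

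**3. Illustration of size, with no EMDR effect at all.** The article gives no figures for this, so the inputs are assumptions: test-retest correlation r of 0.6 to 0.8, patients entering k = 0.5 to 1.0 SD above their usual level, equal SDs at both times, two-sided alpha 0.05, 200 complete pairs, no clustering by therapist.

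- Regression to the mean in SD units = k(1 − r)
- Standardised paired change d_z = k(1 − r) / √(2(1 − r))
- Power of the paired t-test: noncentral t, 199 degrees of freedom, noncentrality d_z × √200

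| r | k | Change (SD) | d_z | Probability of p < 0.05 |
|---|---|---|---|---|
| 0.8 | 0.5 | 0.2 × 0.5 = 0.10 | 0.10/√0.4 = 0.16 | 60% |
| 0.7 | 0.5 | 0.3 × 0.5 = 0.15 | 0.15/√0.6 = 0.19 | 78% |
| 0.6 | 0.5 | 0.4 × 0.5 = 0.20 | 0.20/√0.8 = 0.22 | 88% |
| 0.8 | 1.0 | 0.2 × 1.0 = 0.20 | 0.20/√0.4 = 0.32 | 99% |
| 0.7 | 1.0 | 0.3 × 1.0 = 0.30 | 0.30/√0.6 = 0.39 | over 99.9% |
| 0.6 | 1.0 | 0.4 × 1.0 = 0.40 | 0.40/√0.8 = 0.45 | over 99.9% |

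If total non-specific change from all sources were only d_z = 0.1, the probability would be 29%.

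**4. What 200 does provide.** The paired change detectable with 80% power is d_z of about 0.20. That is good precision on change. A larger sample would narrow the interval around the same mixture and leave its composition as it is.

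**5. Terms used for predictors.** The abstract and section 2.1 speak of prognostic factors. Sections 1.1, 4.1.1, 4.1.3 and 4.2 speak of predictors of treatment response or success. A single arm supports the first term.

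**The case against.** The strongest defence is that the article mostly frames itself correctly. It is labelled exploratory, the sample size rests primarily on feasibility, section 4.2 makes a dataset the primary aim, no success criterion is set, and the Discussion leaves larger-scale testing of efficacy to future studies. An uncontrolled naturalistic cohort is a legitimate design for that purpose, and the article already collects analgesic use, medication change and additional treatments. All of this stands. It limits the point to the claims and leaves the design alone. It does not cancel the claims: efficacy is listed as a reason for the sample size in the same section that calls the study exploratory, and no sentence in the article says that change cannot be attributed to EMDR.

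Several stronger readings are tempting but unsupported:

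- *A positive result is all but certain.* At the lower end of the assumed range the probability is about 60%, and the assumed entry shift has no support in the text, which sets no pain-intensity threshold for entry.
- *An inflated Cohen's d will size the randomised trial.* The article says the results should show whether recruitment, data quality and standardisation suffice. It nowhere says that d will be used for sample size.
- *The article fixes T0 to T1 as the contrast.* Section 4.2 names none. T0 to T1 is an inference from the single cohort and Table 1, though any contrast from T0 has the same limit.
- *The personalised-treatment sentence is a planned analysis.* It is an outlook in the Discussion. Predicting outcome under treatment is something one cohort can do.
- *An extra measurement just before the first EMDR session would solve the problem.* That phase has no defined length and may be very short, regression to the mean would fall mostly in it, and the contrast would still not separate EMDR from the psychotherapy around it.

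**Conclusion.** The point holds as a mismatch between the design and what the article says it can deliver. Sections 2.4.2, 2.5 and 4.2 attribute efficacy, benefit or effectiveness to EMDR from a cohort in which change cannot be attributed to EMDR, and sample size cannot supply that attribution. This rests on the article's own statements and not on detail left to an analysis plan.

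The size of the non-specific change cannot be known from the document. Under the assumed inputs, regression to the mean alone would give d_z of about 0.16 to 0.45, significant about 60% to over 99% of the time with 200 complete pairs. The logical point does not depend on those figures. On predictors the conclusion is narrower: the analyses can identify prognostic factors for outcome under treatment, but cannot show who responds to EMDR specifically.

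**What to change.** In sections 2.4.2, 2.5 and 4.2:

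1. Replace efficacy, therapeutic benefit or effectiveness of EMDR with *uncontrolled within-patient change during psychotherapy that includes EMDR*.
2. In 2.5, remove efficacy from the reasons for 200 patients; keep feasibility and the description of side effects.
3. In 4.2, describe the predictor analyses as prognostic factors for outcome under treatment, in line with the abstract and section 2.1.
4. State once that attribution of change to EMDR, and moderation of its effect, need the later randomised trial.

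As a minor point, section 2.4.1 says that patients "must be commencing therapy with a therapist participating in this network" and also that psychotherapy has already begun. The two sentences should be reconciled, because they determine how much psychotherapy precedes T0.

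The cost is a few sentences and more modest claims. Treatment, assessments and recruitment are unchanged.

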## Advancing implementation of EMDR in clinical practice

3

Therapists participating in the study will be recruited via the EMDRIA Germany or will be referred by other participating therapists. Additionally, the project will presented at national and international conferences, gaining exposure to a broader audience, and an article about the project has been published in the EMDRIA journal. The study is open to all psychotherapists and physicians with formal psychotherapeutic training and accredited EMDR certification.

To promote the implementation of EMDR in pain therapy, the network emphasises supporting the application of EMDR in pain management according to scientific standards. This is achieved by providing validated EMDR treatment protocols free of charge (see Supplementary material) and offering practical working materials for therapists. These measures not only enhance the appeal of network membership but also encourage the standardisation of treatment approaches and facilitate the specialisation of EMDR therapists in treating patients with complex pain disorders.

Additionally, the network has launched a virtual platform where therapists can connect, share experiences, and participate in bimonthly online peer supervision meetings. During these meetings, they discuss complex patient cases and receive supervisory feedback. The platform is supplemented by a regularly updated newsletter that informs about the latest developments, research findings, and relevant events in the field of pain therapy. The newsletter provides lay-friendly summaries of current scientific studies and contextualises them within the clinical setting, thus aiding the translation of scientific knowledge into clinical practice.

## Outcomes

4

### Patients variables

4.1

#### Treatment outcomes and efficacy

4.1.1

In this study, we aim to identify factors that predict a significant treatment response to EMDR therapy for chronic pain. We will follow established recommendations for outcome measures in clinical chronic pain trials and recommendations for interpreting clinical importance of group differences [Initiative on Methods, Measurement, and Pain Assessment in Clinical Trials, IMMPACT (Dworkin et al., 2008; Turk et al., 2003)]. Core outcome domains include pain intensity, physical functioning, emotional functioning, stress experience, and both patient and therapist ratings of patients improvement and satisfaction.

The effectiveness of EMDR therapy will be quantified by determining effect sizes and response and non-response rates on various outcome variables.

#### Patient perception of change

4.1.2

Global ratings of change of the overall situation due to treatment was evaluated using the Patient Global Impression of Change (PGIC) scale, which is a single-item rating on a 7-point scale ranging from “very much improved” to “very much worse” (Ferguson and Scheman, 2009). Changes of “much improved” and “very much improved” are considered as clinically relevant. Similarly, therapists should perceive that at patients show at least 60% of improvement, as measured by a score of greater than or equal to 5 on the Therapist Global Impression of Change Scale (TGIC).

#### Predictors of treatment outcome

4.1.3

A multidimensional phenotyping of patients will be performed, including various aspects such as clinical symptoms, psychological comorbidity, personality factors, therapy expectations and functionality. The aim is to identify predictors that can be used to predict treatment success or failure.

#### Evaluation of feasibility and practicability

4.1.4

The EMDR Pain Network will evaluate the structures and processes of the network for conducting larger multi-centre clinical trials. This will include the assessment of inclusion rates per therapist, the quality of documentation of outcome variables, and patient satisfaction with the adjunctive evaluation.

#### Adverse effects associated to EMDR therapy and safety outcomes

4.1.5

1. Negative Effects: These are intended to be captured using the Negative Effects Questionnaire (NEQ) and the Inventory for Assessing Negative Effects of Psychotherapy (INEP).

2. Severe Adverse Events (SAEs): These will be documented and examined for potential causal relationships with EMDR therapy.

#### Comprehensive assessment

4.1.6

Table 1 shows all measures used during the different points of data acquisition. In addition to the assessment of core-outcome domains, an extensive baseline assessment is performed using standardised and validated questionnaires (see Table 1). The aim is to identify possible predictors in the areas of psychological comorbidity (anxiety, depression, somatization and sleep disorders), catastrophizing, fear of illness and fear avoidance behaviour, past stress experiences and post-traumatic distress, therapy expectations and therapy experience, as well as individual coping and resilience factors.

These defined criteria should not only capture the direct benefits and tolerability of EMDR therapy in chronic pain patients, but also contribute to the optimization of therapeutic approaches and the improvement of treatment quality.

### Statistical analyses overview

4.2

The primary aim of the ‘EMDR Pain Therapy Network’ is to generate a high-quality dataset that facilitates the investigation of future effectiveness measures, response rates, and potential predictors for both response and non-response. This dataset will provide broad opportunities for exploratory analyses to address future research questions. Within the network, specific questions and analyses are pre-planned:

Descriptive Analysis: To characterise the sample, descriptive statistics will be employed, covering demographic data, clinical characteristics, and outcome criteria. Continuous variables will be described using means, standard deviations, medians, and interquartile ranges. Categorical variables will be presented through frequencies and percentages.Effectiveness Outcome Analysis: The effectiveness of EMDR therapy will be evaluated by calculating effect sizes using Cohen’s d, with t-tests to determine these values. Response and non-response rates will be analysed using binary logistic regressions, with the PGIC and TGIC scales as dependent variables.Adverse effect Outcome Analysis: Adverse effects will be quantified through frequency analysis for each item of the NEQ questionnaire, and serious adverse events (SAEs) will be described using descriptive statistics, analysing their correlation with EMDR therapy.Therapist Influence: The impact of therapists on treatment outcomes will be explored using multivariate models or regression analyses, considering various contextual factors such as different therapy approaches, therapist experience.Analysis of predictors: Predictors for therapy success will be identified through multivariate regression analyses, using data from multidimensional phenotyping as independent variables.Feasibility and Practicability Assessment: The practicability of the evaluation process will be assessed by analysing dropout rates, missing values, and the variability of inclusion rates per therapist. An intention-to-treat analysis will be conducted, and satisfaction with the evaluation will be measured using z-scores.

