### Objectives

1.1

The ‘EMDR Pain Network Germany’ was founded with the aim of promoting and further developing the quality and scientific evidence of EMDR in pain therapy in accordance with the current state of research and to support the exchange between clinicians and thus promote and scientifically accompany the implementation of EMDR in the therapy of chronic pain. This network is a scientific cooperation project under the direction of the Department of General Internal Medicine and Psychosomatics at Heidelberg University Hospital in collaboration with the professional association EMDRIA Deutschland e.V. and the EMDR Institute Germany. It aims to facilitate (1) longitudinal research into the therapeutic effects of EMDR in the treatment of chronic pain at an individual level, including adverse effects, (2) the identification of potential predictors of individual response/non-response to treatment between participants, and (3) the facilitation and scientific monitoring of the implementation of EMDR in pain therapy.

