### Procedure

2.3

Outpatient therapists will identify patients with chronic pain conditions for whom they would like to provide an EMDR intervention as part of their regular psychotherapy. In a first step, these patients will be informed by the therapists and will give their written consent to be contacted by the study team at the University Hospital of Heidelberg. There will be no specific recruitment; rather, therapists will decide which patients to admit for outpatient therapy and which to report to the EMDR network. Within a further diagnostic appointment, the Structured Clinical Interview for the Diagnostic and Statistical Manual for Mental Disorders (SCID-5) (First et al., 2015) will be conducted by trained research assistants via telephone. Figure 1 illustrates the subsequent steps of data acquisition, which will be conducted online using the web application REDCap (Harris et al., 2019). First, eligible patients undergo a comprehensive baseline assessment (T_0_), including a broad range of self-rating instruments on various domains of relevant symptomatology, physical and emotional functioning, and other potential mechanistic and predictive factors. When patients and therapists decide to end the therapy, we will conduct a post-treatment outcome assessment (T_1_) including main outcomes, relevant measures from the baseline assessment, therapeutic alliance, therapy evaluation, and potential adverse effects associated with the treatment. Finally, three follow-up assessments (T_2_–T_4_) will be implemented 4 weeks and 3 months and 12 months post-treatment.

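### The effectiveness analysis fixes t-tests and binary logistic regression, which cannot estimate the individual-level course over T0 to T4 that aim (1) names

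*Protocol article*

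**What the plan says.** Section 1.1 (Objectives) gives as its first aim "longitudinal research into the therapeutic effects of EMDR in the treatment of chronic pain at an individual level, including adverse effects". Section 5 (Discussion) says of the framework: "It enables longitudinal analyses that describe the course of treatment success and identify individual differences in outcomes".

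The schedule supports this. T1 falls at the end of therapy (section 2.3: "When patients and therapists decide to end the therapy, we will conduct a post-treatment outcome assessment"), and the three follow-ups "will be implemented 4 weeks and 3 months and 12 months post-treatment". Table 1 places SF-12, HADS, MPI-D and ODI at T0, T1 and T2–T4, and the PGIC at T1 and T2–T4. Table 2 places the TGIC at T1 only.

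For effectiveness, section 4.2 fixes two methods. The first is "The effectiveness of EMDR therapy will be evaluated by calculating effect sizes using Cohen’s d, with t-tests to determine these values". The second is "Response and non-response rates will be analysed using binary logistic regressions, with the PGIC and TGIC scales as dependent variables". It does not say which visits the t-tests compare. The feasibility item of the same section announces an intention-to-treat analysis and plans to examine dropout and missing values, but links neither to a method for the effectiveness estimate.

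**The concern.** The stated estimator does not match the stated aim. Five occasions are collected per patient, and the effectiveness item uses a method built for two. Even with complete data, a set of t-tests gives separate contrasts. It does not give a model of the course, and it says nothing about how much courses vary between patients. The logistic regressions do not fill the gap. The TGIC exists at one visit only, and nothing in the text treats the PGIC as a repeated measure.

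The second issue is incomplete follow-up. A paired t-test uses only patients observed at both visits, so each follow-up contrast may rest on a different group. Whether benefit lasts to 12 months is a main reason for running three follow-up waves, and section 2.5 wants the results of the first 200 patients to inform a larger trial. If loss depends on outcome, the 12-month effect size passed on to that trial could be wrong in either direction.

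**Working it through.** **Step 1: the plan's own figure.** Section 2.5 requires at least 20 therapists with at least 10 patients each: 20 × 10 = 200. This reproduces. The documents give no attrition rate, correlation, SD, effect size or decay, so everything numerical below is an assumption, shown as a range.

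**Step 2: method against aim, without any dropout assumption.**

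| Needed for aim (1) | Supplied by the effectiveness item |
|---|---|
| Course over T0, T1, T2, T3, T4 | Two-occasion contrasts, visits not named |
| Spread of courses between patients | Not estimated |
| Use of patients with some visits missing | Not possible with a paired t-test unless values are imputed; no method stated |
| Response over follow-up | TGIC at T1 only; PGIC at T1–T4, but no repeated-measures form stated |

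**Step 3: how many patients a paired T0–T4 test would use.** n at T4 = 200 × (1 − loss)^4, rounded at each wave. The half-width of the 95% interval for d is approximately 1.96/√n.

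| Assumed loss per wave | n at T4 | Half-width |
|---|---|---|
| 5% | 162 | 0.154 |
| 10% | 131 | 0.171 |
| 15% | 104 | 0.192 |
| 20% | 82 | 0.216 |
| 30% | 48 | 0.283 |

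**Step 4: bias by dropout mechanism.** Simulation with 200 patients, five occasions, unit SD and within-patient correlation 0.6. True change from T0 is -0.50, -0.45, -0.35 and -0.25 SD at T1 to T4. Loss is permanent, with a base rate of 5, 10 or 20% per wave and a log-odds slope of 0.5 or 1.0 per SD where loss depends on outcome. There were 300 runs per setting. The estimates are for T4 minus T0; the truth is -0.25.

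| Loss depends on | Paired, 5% | Paired, 10% | Paired, 20% | Likelihood model, all rates |
|---|---|---|---|---|
| Nothing | -0.248 | -0.251 | -0.254 | -0.247 to -0.256 |
| Less gain at previous visit | -0.282 to -0.329 | -0.309 to -0.378 | -0.367 to -0.474 | -0.247 to -0.259 |
| Higher symptom level at previous visit | -0.241 to -0.231 | -0.228 to -0.208 | -0.209 to -0.194 | -0.248 to -0.261 |

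**Step 5: a second set of assumptions.** 160 patients at T1, loss only after T1, correlation 0.5 to 0.7, and 57 to 74% of them retained at T4. When patients with less gain leave, the paired T4 estimate is -0.29 to -0.46 and its 95% interval covers the truth in 45 to 91% of studies. The apparent fading from T1 to T4 is 0.04 to 0.21 SD, against a true 0.50 − 0.25 = 0.25. When loss follows the previous symptom level, the bias is essentially nil in this setting. In step 4 that mechanism also acted before T1, which is why it produced some understatement there.

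**The case against.** A fair opponent would make four points.

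1. *Section 4.2 plans more than two methods.* This is correct. It also lists descriptive statistics, regressions for predictors and, on therapists, "The impact of therapists on treatment outcomes will be explored using multivariate models or regression analyses". A reader might infer that nothing but t-tests and logistic regression is planned; that holds for the effectiveness item alone. The other models address predictors and therapists, and none is said to model visit or course.

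2. *The section is an overview in a condensed article on an exploratory evaluation.* Covariance structure, visit contrasts and missing-data handling are commonly left to an analysis plan, and their absence is no finding. What remains is that the estimator is stated. An analysis plan that follows section 4.2 would still use t-tests.

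3. *Intention-to-treat is announced, and t-tests can be run on imputed data.* This is also true. A reader might infer that the durability result will come from shrinking, self-selected subsets. The documents do not support that forecast: they give no attrition rate, no complete-case rule and no T2–T4 contrast. Equally, the intention-to-treat sentence does not resolve the matter, because it sits under feasibility and names no way to include a patient whose follow-up is missing.

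4. *The bias is assumed, and the likelihood model is favoured by how the data were simulated.* The first part stands in full: both size and direction depend on the mechanism. The second stands as a limit, since loss in every simulation depended only on observed values, which is what that model requires.

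It can also be said that the aims speak of facilitating and enabling longitudinal work and do not commit to it. That softens the mismatch. Still, aim (1) is the network's first stated purpose, and section 4.2 presents its list as analyses already planned.

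**Conclusion.** The point holds as a mismatch between a fixed method and the first stated aim. With or without dropout, two-occasion t-tests cannot describe the course over five visits or the differences between patients in that course. This part rests on no assumption.

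The effect of missing follow-up is conditional. It assumes that the t-tests are paired comparisons with T0 made without imputation, which is the natural reading but is not stated. Against an assumed true 12-month change of -0.25 SD, the paired estimate is unbiased under outcome-unrelated loss. It is about -0.28 to -0.47 when patients with less gain leave, and unbiased or down to about -0.19 when loss follows symptom level. The documents do not show which of these applies, so it cannot be said that the plan will overstate lasting benefit. The likelihood model's advantage holds where loss depends on observed values; if it depends on unobserved ones, that model can be biased too.

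The change is worth making because it is cheap and the results are meant to guide a larger trial. In an exploratory evaluation it is not a fatal flaw.

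**What to change.** In section 4.2, make the effectiveness estimator a linear mixed model for repeated measures, one for each core outcome scheduled to T4: SF-12, HADS and one named MPI-D scale (the inventory has 12, so the scale must be chosen in advance).

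- Visit (T0, T1, T2, T3, T4) as a factor, unstructured within-patient covariance, and a random effect for therapist, since patients are nested in at least 20 therapists.
- Include every patient with any assessment, and state that this is how the intention-to-treat analysis is carried out.
- Report T1, T2, T3 and T4 minus T0, and T4 minus T1, with 95% intervals, and also express them as standardised effect sizes.
- Describe individual courses in a separate model with random intercepts and slopes. Patient random effects should not be added to the unstructured-covariance model, which already absorbs the within-patient variation. State the time axis, because T1 falls when therapy ends and not at a fixed interval after T0.
- Analyse the PGIC at T1–T4 with a mixed logistic or ordinal model. The TGIC stays a single-visit analysis at T1.
- Keep the t-tests as description.

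Cost: a change of wording and a little more analysis work, with no new patients, visits or data. The downside is reliance on a missing-at-random assumption, which should be stated.
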